## Abstract

**Background:**

The practice of traditional Chinese medicine (TCM) has a profound history in many Asian countries. TCM syndrome is a set of characteristic physical signs and symptoms shared by a group of patients. Syndrome diagnosis and treatment assignment according to the identified TCM syndrome is a long-held practice of Chinese medicine. Owing to its distinctive way of interpreting illness and administering care, medical practitioners not well educated in TCM theories and practices are generally incapable of giving out prescriptions for Chinese patent drugs. Currently, the existence of a multitude of Chinese patent drugs marked with largely identical indications is further complicating this situation.

**Methods:**

In this multicenter, randomized, controlled, double-blind, double-dummy clinical trial, in which we will use the comparative effectiveness research method, we will compare the efficacy of two commonly used Chinese patent medicines for angina patients diagnosed with qi deficiency and blood stasis syndrome. A total of 160 patients will be recruited and randomly assigned to receive either (1) QiShenYiQi dripping pills, Tongxinluo placebo and routine medication or (2) Tongxinluo capsules, QiShenYiQi placebo and routine medication. These treatment regimens will be carried out for 4 weeks, followed by a 10-day washout period and a 4-week crossover phase in which the treatments in the two patient groups will be exchanged. Patients will be allowed to choose symptoms that matter most to them and will be grouped accordingly. Patient-reported outcomes such as the Seattle Angina Questionnaire score and the 15-point Likert scale score will be measured and reported. The minimally clinical important difference will be calculated and used for efficacy assessment, and correspondence analysis will be performed to identify the best indications for each drug.

**Discussion:**

The goal of the study is to establish a methodology for the precise identification of the characteristic indications for which a Chinese patent drug is most effective. The findings of this study will inform the practicality of the proposed evaluation method.

**Trial registration:**

Chinese clinical trials register Chi CTRTTRCC13003732

## Background

### Traditional Chinese medicine interpretation of angina and therapeutic rules

Syndrome differentiation, also termed *pattern diagnosis* (*Bian Zheng* in Chinese pinyin), is one of the kernel theories of traditional Chinese medicine (TCM). The TCM syndrome, or *Zheng*, is a characteristic profile of clinical signs and symptoms manifested by a group of patients. The clinical efficacy of Chinese medicine relies heavily on the correct diagnosis of a specific TCM syndrome. According to the 2002 Guidelines for Clinical Research of Chinese Medicine (new drug) [1] released by the Chinese Food and Drug Administration patients with angina pectoris can be diagnosed on the basis of any one of the following eight TCM patterns: (1) qi deficiency and blood stasis syndrome, (2) heart blood stasis obstruction syndrome, (3) qi stagnation and blood stasis syndrome, (4) syndrome of phlegm obstruction in the heart vessel, (5) syndrome of congealing yin cold, (6) dual-deficiency of qi and yin syndrome, (7) heart and kidney yin deficiency syndrome and (8) yang qi debilitation syndrome. Among these criteria, the qi deficiency and blood stasis syndrome is most typically observed in Chinese angina patients.

For the management of angina pectoris patients with qi deficiency and blood stasis syndrome, herbal remedies intended to invigorate qi, activate blood circulation and transform stasis will be administered. The main function of the herbal remedy is to improve clinical signs and symptoms of the patients.

### Comparative effectiveness research and traditional Chinese medicine

The concept of comparative effectiveness research (CER) was initiated in the 1990s by Mark Boutin, the deputy executive president and chief operating officer of the US National Health Council [2]. In the years that followed, CER has been used to aid public health policy-making and introduced into the field of clinical research in a number of countries [3]. In May 2011, Claudia M Witt (Institute of Social Medicine, Epidemiology and Health Economics, Charité University Medical Center, Berlin, Germany) proposed introducing CER techniques into TCM research at the sixth annual meeting of the International Society of Complementary Medicine Research [4].

### Efficacy evaluation based on patient-reported outcomes

A patient-reported outcome (PRO) is a report directly from the patient, without influences from doctors or others, about how they function or feel in relation to their health status and the treatment they are receiving [5]. The PRO measurement tools are developed to provide insights from the patient’s perspective regarding the impact of therapeutic interventions on their health. Patient-important outcomes (PIOs) are a selection of outcome measures that are considered most relevant to the patients. Examples of PIOs include pain, fatigue, quality of life and death. Efforts to assess PIOs for a particular disease or condition and to promote the use of PIOs in clinical research settings facilitate effective interpretation of the results by emphasizing the evaluation of treatment effectiveness. The integration of PIOs and PROs into Comparative Effectiveness Research could be a useful tool for the assessment of outcomes requiring patients’ subjective perceptions and judgments, such as consumer satisfaction and health-related quality of life [6].

### Minimal clinically important differences and patient-reported outcome measurements

Minimal clinically important differences (MCIDs) are self-perceived scores that signify clinically significant improvements in PROs that can be used to identify the minimal changes in a specific aspect of a patient’s health [7], and it is believed to reflect the smallest change in the PRO evaluations of a clinical intervention that is meaningful to the patient.

Distribution-based methods for the determination of MCIDs have been widely used and can be subdivided into the effect size (ES) and the standard error of measurement (SEM). The latter measurement is particularly recommended for its relative independence from sample source and stability across different studies [8,9]. In our present study, changes in PROs will be calculated using the SEM, which will represent patients’ self-reported improvements in symptoms or health-related function.

### Traditional Chinese medicine for angina pectoris due to coronary heart disease

Angina pectoris is one of the most common symptoms of coronary heart disease (CHD) and afflicts a large portion of CHD patients. It has been found over the course of years of clinical practice that TCM is effective in treating angina. Because the qi deficiency and blood stasis syndrome together have been identified as a major TCM syndrome among patients with angina, in this CER study we will select two Chinese patent drugs most frequently used for treating angina patients diagnosed with this common syndrome. The patent drugs to be compared are QiShenYiQi (QSYQ) dripping pills (Tasly Pharmaceutical Co Ltd, Tianjin, China) and Tongxinluo (TXL) capsules (Yiling Pharmaceutical Co Ltd, Shijiazhuang City, China). QSYQ pills are composed mainly of *Radix Astragali*, *Radix Salvia miltiorrhiza*, *Radix Notoginseng* and *Lignum Dalbergia Odorifera*. TXL capsules are an herbal mixture of *Radix Ginseng*, Hirudo, Quan Xie *Eupolyphaga seu Steleophaga*, *Scolopendra*, Periostracum Cicadae, Radix Paeoniae rubra, Lignum Santali Albi, *Lignum Dalbergia Odorifera*, frankincense, *Semen Ziziphi spinosae* and borneol.

## Objectives

We are conducting a multicenter, randomized, controlled, double-blind, double-dummy clinical trial to compare the effectiveness of two Chinese patent medicines for angina patients diagnosed with qi deficiency and blood stasis syndrome. The ultimate goal is to test the proposed methodology for the individualized evaluation of the therapeutic effects of Chinese patent drugs and for distinguishing between drugs targeting a multitude of similar indications.

To fulfill these objectives in our present study, we highlight the introduction of trial participants’ therapeutic needs and willingness in terms of group allocation and the use of CER methodology. Specifically before being entered into the randomization process, all eligible participants with qi deficiency and blood stasis syndrome will first be allowed to choose from among four prespecified groups of symptoms which they would most like to be addressed. The outcomes for these symptoms are considered PIOs and will be assessed using PRO instruments. Furthermore, we will test the use of the CER method to compare the curative effects of QSYQ dripping pills and TXL capsules, two widely used Chinese patent medicines for angina patients with qi deficiency and blood stasis syndrome. By analyzing and comparing the effects of the two drugs for each symptom group, we aim to summarize the characteristics of the drugs’ curative effects and identify the best targeted indications for each drug.

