### Patient grouping and treatment allocation

Using stratified and blocked randomization, we will first categorize eligible participants into four groups on the basis of their varied choice of secondary symptoms to be addressed, and then we will randomly assign them to one of the two treatment arms at a ratio of 1:1. To minimize imbalances across groups, gender will also be used as a stratification factor. The random number sequence will be generated by a third-party statistician using SAS version 9.1 software (SAS Institute, Cary, NC, USA).

The four symptom combination groups, each representing the signs a patient most wishes to bring under control, were formed according to the characteristic physical manifestations of the qi deficiency and blood stasis syndrome defined in the 2002 Guidelines for Clinical Research of Chinese Medicine (new drug). The grouping criteria for patients with varying therapeutic needs resulted in the following four symptom combination groups:

1. Combination 1: chest pain + chest tightness + shortness of breath

2. Combination 2: chest pain + chest tightness + fatigue

3. Combination 3: chest pain + chest tightness + palpitations

4. Combination 4: chest pain + chest tightness + spontaneous perspiration

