### Measurement tools and time of data capture

The SAQ and 15-point Likert scale scores will be used to collect PROs immediately following the first treatment period and the crossover treatment period. The minimal clinically important differences (MCIDs) of the SAQ and the Likert scale scores at these two time points will be calculated for efficacy evaluation and comparison.

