**Figure 2 F2:**
[figure not shown]
**Calculation of the M value.** SAQ, Seattle Assessment Questionnaire.

1.a.i. Find patients receiving treatment A (or treatment B) whose self-reported Likert scores are within the range of +2 to +3.

1.a.ii. Collect the corresponding SAQ score of these patients, use X_1_ to refer to it and calculate the mean value $X{\left(—\right)}_{1}$.

1.a.iii. Find patients receiving Treatment A (or Treatment B) whose self-reported Likert scores are within the range of 0 to +1.

1.a.iv. Collect the SAQ scores of these patients, use X_0_ to refer to it and calculate the mean value X_0_

1.a.v. $M_{0}=X_{0}-X{\left(—\right)}_{0}$

1.a.vi. $M_{1}=X_{1}-X{\left(—\right)}_{1}$

2. Calculation of SEM (SEM_0_ and SEM_1_) [7,12,13].

$$\mathrm{SEMO}=\sqrt{\sum M0^{2}/\left(n-1\right)}\times \sqrt{1-r}$$

$$\mathrm{SEM}1=\sqrt{\sum M1^{2}/\left(n-1\right)}\times \sqrt{1-r}$$

n:sample size; r:the reliability coefficient of SAQ

3. Calculation of MCID We will calculate the MCIDs for treatment A (referred to as MCID1) and treatment B (referred to as MCID2) during the first treatment period and for treatment A (referred to as MCID3) and treatment B (referred to as MCID4) during the crossover period.

MCID, Minimal clinically important difference; SEM, Standard error of measurement.

$$\mathrm{MCID}\;=\;\sqrt{\mathrm{SEM}O^{2}+\mathrm{SEM}1^{2}}$$

4. Individualized efficacy evaluation upon the first round of treatment: Treatment interventions will be defined as either effective or ineffective by comparison of the patient’s personal SAQ score with the calculated MCID value.

4.a. Treatment A will be defined as effective if a patient receiving it has a SAQ score greater than the MCID1 score.

4.b. Treatment B will be defined as effective if a patient receiving it has a SAQ score greater than the MCID2 score.

4.c. A treatment will be adjudged ineffective if a patient receiving it reports a SAQ score lower than the corresponding MCID value (MCID1 or MCID2).

5. Individualized efficacy evaluation upon crossover of treatment: Because of the complexity of the study design, all the patients will be categorized into four groups by using the following assessment tools:

5.a. Group 1: Both treatments A and B are effective for patients in this group:

5.a.i. For patients who first receive treatment A and then treatment B, the first SAQ score > MCID1 and the second SAQ score > MCID4

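### No named measure of the patient's chosen secondary symptom enters the effective/ineffective rule, so the efficacy tables show SAQ response by symptom preference

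*Protocol article*

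**What the plan says.** All references are to the protocol article.

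- **Promise (Objectives).** Before randomization, patients choose the symptom group they most want treated. Of the chosen symptoms the text says: "The outcomes for these symptoms are considered PIOs and will be assessed using PRO instruments".
- **Aim (Objectives).** "By analyzing and comparing the effects of the two drugs for each symptom group, we aim to summarize the characteristics of the drugs’ curative effects", leading to a best indication for each drug.
- **Groups (Patient grouping and treatment allocation).** The plan will "categorize eligible participants into four groups on the basis of their varied choice of secondary symptoms to be addressed". The first and last groups read "Combination 1: chest pain + chest tightness + shortness of breath" and "Combination 4: chest pain + chest tightness + spontaneous perspiration". The two between them replace the last element with fatigue or palpitations.
- **Instruments (Measurement tools and time of data capture).** On what is recorded and when, this section says: "The SAQ and 15-point Likert scale scores will be used to collect PROs immediately following the first treatment period and the crossover treatment period". No other patient-reported instrument is named.
- **Rule (Efficacy assessment tools, items 4 and 5).** For the first period: "Treatment A will be defined as effective if a patient receiving it has a SAQ score greater than the MCID1 score". The same form is used for treatment B and for the crossover period, with MCID2 to MCID4.
- **Use (Tables 1 and 2; Correspondence analysis).** Patients are counted by symptom combination and by the four classes from that rule. The nearest row and column points in the biplot are read as the drug's characteristic indication.

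**The concern.** The rows of Table 1 are defined by the secondary symptom a patient wants relieved. The columns are defined by a score that makes no reference to that symptom. If TXL falls nearest to the perspiration row, for example, the natural reading is that TXL suits perspiration. What was observed is that patients who named perspiration as their priority more often passed an SAQ threshold on TXL and not on QSYQ. These are different statements, and the Objectives promise the first.

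At stake is the trial's main product: a method for telling apart two drugs with nearly the same indications by the symptom each treats best.

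**Working it through.** The plan gives no figure for this point, so the check is to follow the chosen symptom through the algorithm and see where it is used.

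**Step 1. What distinguishes the rows.** Every combination is chest pain + chest tightness + one further symptom. The further symptom is the only element that varies, so any contrast between rows is a contrast by that symptom.

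**Step 2. How the threshold is built (Efficacy assessment tools, items 1 to 3).**
- For a given treatment and period, take patients with Likert scores of +2 to +3 and collect their SAQ scores X1. Take those with Likert scores of 0 to +1 and collect their SAQ scores X0.
- M1 and M0 are the deviations of X1 and X0 from their own means.
- SEM0 = √(ΣM0²/(n−1)) × √(1−r), and SEM1 likewise, with r the reliability coefficient of the SAQ.
- MCID = √(SEM0² + SEM1²).

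The inputs are SAQ scores, the SAQ reliability and a Likert band that decides whose SAQ scores count. The bands are formed by treatment, not by symptom combination. There are 2 treatments × 2 periods = 4 thresholds (MCID1 to MCID4) and none specific to a combination.

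**Step 3. How a patient is classified (items 4 and 5).** The class depends on the treatment sequence, the first SAQ score, the second SAQ score and the two relevant MCIDs. Neither the combination nor any rating of the secondary symptom is an input. Two consequences follow:
- Two patients in Combination 4 with the same sequence and the same SAQ scores receive the same class, even if perspiration has stopped in one and is unchanged in the other.
- Moving a patient from Combination 1 to Combination 4 changes the row in which that patient is counted, but not the class.

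**Step 4. What the tables hold.** Table 1 has 4 rows, one per combination. Table 2 has 6 pairs + 4 triples + 1 quadruple = 11 rows, each a sum of Table 1 counts. All 4 + 11 = 15 rows are filled by the rule in Step 3.

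**Step 5. What is concluded.** The correspondence analysis takes both tables as input, so a distance in the biplot can only reflect how SAQ-based classes are distributed over preference groups. The step from there to the drug's indication for a particular symptom is not supported by any quantity in the algorithm.

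**Step 6. Consistency with the rest of the plan.** The Sample size calculation is also based on SAQ change alone, with no symptom-specific outcome.

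**The case against.** **The Likert scale may already ask about the chosen symptoms.** Its wording is not given, and an article may well leave item wording to the full protocol. This stands, and it rules out one reading that a reader might infer: that the trial never measures relief of the chosen symptom. The document does not establish that. It does establish that, whatever the Likert scale asks, its score does not enter the classification directly.

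**The Likert score is used in efficacy evaluation, because it helps to set the MCID.** True. The measurement section also announces MCIDs for the Likert score itself, but the rule that follows uses none. The Likert score acts only by selecting whose SAQ scores form a threshold, so one patient's symptom relief does not decide that patient's own class.

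**The SAQ may reflect part of what each group wants.** Chest pain and chest tightness are two of the three symptoms in every combination, and the article does not list the SAQ items. This stands too. The point therefore rests on one common score being applied identically in all groups, not on what the questionnaire contains.

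**Comparing two drugs on a common outcome across patient profiles is legitimate, and the study calls itself exploratory.** Agreed. It can show which profile responds better to which drug on the SAQ. A reader might conclude that the trial's aim cannot be answered at all; that is too strong. The gap lies in attributing benefit to the secondary symptom.

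**Could the loss be expressed as power?** A reader might take the pilot difference of 2 ± 2.5 as a standardized effect (2/2.5 = 0.8) on the chosen symptom and shrink it by an assumed correlation with the SAQ. The document does not support this. The pilot figure is already a difference in SAQ change, no correlation is given, and the plan runs no per-combination test of means to which such a power would apply.

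**Conclusion.** The point holds in this form: the Objectives promise assessment of the chosen symptoms and use it to find each drug's best indication, but no named measure of the distinguishing secondary symptom enters the effective/ineffective rule. It affects all 15 rows of Tables 1 and 2 and the correspondence analysis. Those results will show SAQ response by symptom preference; by themselves they do not show which drug relieves which secondary symptom.

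No numerical size can be given. How much is lost depends on how closely SAQ response follows each secondary symptom, on which the document is silent. The conclusion rests only on the rule as written and needs no assumption about SAQ items or Likert wording. Because the rule, the classes and both tables are fully set out, this is a conflict between a specified rule and a stated objective, not a detail left to another document. It should be corrected, but it does not invalidate the comparison of the two drugs on the SAQ.

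**What to change.** 1. At the two planned assessments, have **every** patient rate change in **each** of the four secondary symptoms on the 15-point Likert scale, with reference to the treatment period just ended. If all patients rate the same four symptoms, each symptom can be compared across groups. Since the diagnosis requires only one secondary symptom, include a response for a symptom that was not present, so that its absence is not counted as failure.
2. Prespecify the cut-off for effective on these ratings. One option is +2 or better, in line with the plan's own +2 to +3 band.
3. Build a companion Table 1 from the response on the chosen symptom under each drug, and base symptom-specific indication statements on it.
4. Do not sum responses on different symptoms in a Table 2 layout; such a sum would mix different outcomes under one heading.
5. Keep the existing SAQ tables and their correspondence analysis as the common angina outcome.

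If no ratings are added, reword the aim and the conclusion to SAQ response by symptom preference, and drop statements about which drug relieves which secondary symptom.

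The cost is four single-item ratings at each of two existing assessments (4 × 2 = 8 per patient) and one extra table. No extra visit is needed. The drawbacks are slightly more patient burden and the limited precision of single-item ratings.

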## Methods

### Study design

We will conduct a multicenter, randomized, crossover, double-blind, double-dummy clinical trial. A flowchart of the study protocol is shown in Figure 1.

**Figure 1 F1:**
[figure not shown]
**Study flowchart.** CA, Correspondence analysis; CER, Comparative effectiveness research; MCID, Minimal clinically important difference; PIO, Patient-important outcome; SAQ, Seattle Angina Questionnaire.

## Ethical approval

This study has been approved by the medical ethics committee of Tianjin University of Traditional Chinese Medicine (registration number TJUTCM-EC20130004).

### Setting

Participants will be recruited simultaneously at the cardiology departments of four hospitals in Tianjin City in mainland China.

### Participant recruitment

Potentially eligible angina patients will be provided with general information regarding the trial, the objectives of the research and the rights and obligations of the participants at the first visit. Those who are willing to participate will be asked to give their informed consent to participate before being entered into the screening process. Participants will then be included or excluded according to the predefined inclusion and exclusion criteria.

